### Participant timeline {13}

Study enrollment started on 9 March 2020, and the expected completion date of recruitment is 8 March 2021. Patients will be followed up at 1 month, 4 months, and then every 2 months until 24 months for clinical examination, IOP measurement, OCT imaging of the RNFL/GCIPL, and VF testing (Fig. 2).

**Fig. 2 Fig2:**
[figure not shown]
Study timeline. Clinical examination includes visual acuity measurement, Goldmann applanation tonometry (GAT), and slit-lamp biomicroscopy of the anterior and posterior segments. *OCT* optical coherence tomography, *RNFL* retinal nerve fiber layer, *GCIPL* ganglion cell inner plexiform layer, *GPA* Guided Progression Analysis, *TPA* Trend-based Progression Analysis, *VF* visual field

### Sample size {14}

In our pilot study following 236 glaucoma patients every 4 months for ≥3 years, the mean rate of RNFL thinning was 1.2 μm/year (*P* < 0.001) for eyes with evidence of progressive RNFL thinning detected by TPA; the slope variance was 1.39 (μm/year)^2^ and the residual variance was 3.83 μm^2^ [20]. We aim to detect a difference of at least 0.7 μm/year in the rate of RNFL thinning between treatment groups, given that the mean rate of age-related RNFL thinning has been reported to be approximately 0.5 μm/year [22]. Taking reference from the method of sample size calculation for linear mixed modeling to compare the rates of change of a parameter of interest between two treatment groups described by Ard and Edland [23], 56 patients per study arm are needed for serial RNFL thickness measurements at baseline, 1 month, 4 months, and then every 2 months for 24 months (3 separate measurements will be collected at the baseline, 1-month, and 24-month follow-up visits) with a power of 80% and an alpha of 5%. Assuming a default rate of 10% during study follow-up, a total of 125 patients will be recruited.

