## Data collection and management

### Plans for assessment and collection of outcomes {18a}

Patients will receive a clinical examination, OCT imaging of the RNFL, and VF testing at baseline, 1 month, 4 months, and then every 2 months for 24 months. Three repeated OCT and VF measurements will be collected at the baseline, 1-month, and 24-month visits.

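### The 56 per arm and 80% power assume that three scans taken at one visit are fully independent, which is the most favourable case of an assumption the protocol does not state

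*Protocol article*

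**What the plan says.** Sample size {14} takes its variances from a pilot: "In our pilot study following 236 glaucoma patients every 4 months for ≥3 years". For eyes with progressive thinning, "the slope variance was 1.39" (μm/year)² and "the residual variance was 3.83" μm². The target is stated as "We aim to detect a difference of at least 0.7 μm/year in the rate of RNFL thinning between treatment groups". Using a published sample-size method for comparing slopes in a linear mixed model, it arrives at 56 patients per arm "with a power of 80% and an alpha of 5"%. The schedule is baseline, month 1, month 4 and then every 2 months to month 24, with triplicates included: "3 separate measurements will be collected at the baseline, 1-month, and 24-month follow-up visits". A 10% default allowance raises the total to 125.

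Plans for assessment and collection of outcomes {18a} makes clear that the triplicates are repeats within a visit: "Three repeated OCT and VF measurements will be collected at the baseline, 1-month, and 24-month visits". The Discussion lists this clustering of measurements at the start and end of the trial among the features meant to make an effect detectable in 2 years.

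**The concern.** The residual variance about an eye's fitted line, estimated from visits months apart, can have two parts. One is scan-to-scan error, which differs between scans taken in the same session. The other is anything that moves a whole visit off the line and is therefore shared by all scans of that visit. Three scans at one visit reduce the first part to a third and leave the second untouched. If the whole 3.83 is treated as scan-to-scan error, each triplicate counts as three separate occasions.

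The protocol gives no within-visit correlation, no split of the 3.83 and no number of scans per pilot visit, so the assumption cannot be checked from the text. The power of the primary comparison is at stake. Any shared visit noise lowers it, and no value of rho raises it above the stated figure. The clustered design would then still help, but by less than the calculation credits.

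**Working it through.** **Inputs (Sample size {14}).** Slope difference 0.7 μm/year; slope variance 1.39; residual variance 3.83; alpha 5% (sidedness not stated, taken as two-sided); power 80%; 13 visits at months 0, 1, 4, 6, …, 24; three scans at months 0, 1 and 24, so 19 scans.

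**Formula.** n per arm = 2(1.96 + 0.8416)² × V / 0.7², with V = 1.39 + 3.83/S. S is the sum of squared scan times about their mean, in years².

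**Reproducing the stated figure (19 independent scans).**
- Sum of times 205 months; sum of squares 3751. S = (3751 − 205²/19)/144 = 10.689.
- V = 1.39 + 0.358 = 1.748.
- n = 2 × 7.849 × 1.748 / 0.49 = 56.01. Power at 56 is 80.0%. This matches the protocol.

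**One measurement per visit (13 values).**
- Sum of times 155 months; sum of squares 2597. S = (2597 − 155²/13)/144 = 5.201.
- V = 1.39 + 0.736 = 2.126.
- n = 68.1. Power at 56 = Φ(0.7/√(2 × 2.126/56) − 1.96) = Φ(0.58) = 71.9%.

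The triplicates, taken as independent, therefore save 68.1 − 56.0 = 12.1 patients per arm.

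**Alternatives tried.** A one-sided test gives 44.1 with 19 scans and 53.7 with one per visit. Unweighted visit means of independent scans give 59.6. None gives 56, and the 53.7 also leaves out the triplicates that the text includes.

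**Allowing for shared visit noise.** Let rho be the share of the 3.83 common to a visit. A visit mean of m scans then has variance 3.83 × [rho + (1 − rho)/m]. Weighting each visit by the inverse of that variance gives:

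| rho (assumed) | Residual part of V | V | n per arm for 80% | Power at 56 per arm |
|---|---|---|---|---|
| 0 | 0.358 | 1.748 | 56.0 | 80.0% |
| 0.1 | 0.410 | 1.800 | 57.7 | 78.8% |
| 0.25 | 0.480 | 1.870 | 59.9 | 77.3% |
| 0.5 | 0.580 | 1.970 | 63.1 | 75.1% |
| 0.75 | 0.664 | 2.054 | 65.8 | 73.4% |
| 1 | 0.736 | 2.126 | 68.1 | 71.9% |

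These use the normal approximation. With a t reference the end points are 79.3% and 71.2%.

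**Margin in recruitment.** 2 × 56/0.9 = 124.4, so the 125 is used up by the 10% default allowance.

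**The case against.** The strongest reply is that nothing has been miscalculated: the triplicates are disclosed and 56 follows from the stated inputs. That stands. This is a point about an assumption.

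Second, no document says that the 3.83 contains visit-level noise, and the plan works against some of it. The OCT imaging section has poor-quality, decentred or wrongly segmented scans discarded and repeated at the same visit. Statistical methods {20a} adjusts the primary model for signal strength and for IOP during follow-up. These steps make the upper end of the rho range less likely, but they do not establish rho = 0.

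Third, the effect is bounded. Slope variance is 1.39 of 1.748, about 80% of V, and repeat scanning cannot change it. At rho of 0.25 to 0.5 the loss is about 3 to 5 points.

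Fourth, about 62 to 63 per arm are randomised, and {20c} keeps patients with at least two follow-up visits, so some who default would still contribute. If an average of 62.5 per arm gave complete data, power would be 84.1% at rho = 0 and 76.5% at rho = 1. That is an upper bound, because the surplus was added to cover defaults, and the stated 80% refers to 56.

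A reader might go further and infer that power falls to about 69%, or that the planned model is wrong because it has no visit-level term. The documents support neither. The 69% figure (68.7%) needs rho = 1, meaning no scan-to-scan error at all, together with an analysis that gives every scan equal weight. Section {20a} sets out no random-effects structure, and an article commonly leaves that to the full protocol or SAP.

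**Conclusion.** The concern holds as a point about an unstated and optimistic assumption. With the protocol's inputs, schedule and a two-sided test, 56 per arm and 80% power require same-visit scans to be independent. That is the best case: power at 56 evaluable per arm lies between about 72% and 80%, and is about 75% to 77% for rho between 0.5 and 0.25.

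The range rests on three assumptions: the 3.83 is the variance of a single scan about the eye's line, which is how the protocol's calculation uses it; the analysis weights visits optimally; and 56 patients per arm give complete data. Rho itself is unknown, so no single figure in the range can be called the true power. The working shows an effect on power only, not on type I error or on what the trial estimates.

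**What to change.** In Sample size {14}, state that the calculation treats the three same-visit measurements as independent. Then either give power at 56 evaluable per arm as about 72% to 80% depending on the visit-level share of the residual variance, or estimate that share from test-retest data and report the one matching figure.

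In the primary RNFL model and the VF models, account for repeated scans or tests within a visit, by a visit-within-eye random effect or by visit means with suitable weights. Simple unweighted visit means are less efficient when rho is small (77.5% power at rho = 0 against 80.0%), so the weights matter.

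The cost is a less favourable stated power and one extra variance component. No patients or visits are added.

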### Recruitment {15}

Attending ophthalmologists and investigators will review the clinical records and the RNFL/GCIPL progression analysis reports for glaucoma patients coming back to the eye clinics for scheduled follow-up appointments. Patients with at least 1 year of serial OCT RNFL/GCIPL measurements prior to the recruitment will be checked by the investigators for evidence of progressive RNFL/GCIPL thinning. Those with evidence of progressive RNFL/GCIPL thinning detected by Guided Progression Analysis (GPA) or Trend-based Progression Analysis (TPA) in at least one eye will be invited to attend a screening visit. The principal investigator will explain the study procedures to the patients. Patients who agree to participate in the study will come back on a scheduled visit for baseline investigation.

## Assignment of interventions: allocation

### Sequence generation {16a}

Patients will be randomly allocated (1:1) at the baseline visit to receive NR or placebo within 1 month of enrollment. Randomization with minimization by age (< 60 years vs ≥60 years), gender (male vs female), VF MD (<−6 dB vs ≥ −6 dB), spherical equivalent (<−6.0D vs ≥ −6.0D), mean IOP measurement over the past 3 years (≤21 mmHg vs > 21 mmHg), and number of glaucoma medications (0, 1, 2, 3, or ≥ 4) will be performed using an open-source computer program MinimPy [24]. A random element was introduced in the minimization procedure (i.e., weighted randomization of 0.8) to make the randomization more unpredictable [25]. If both eyes are eligible for inclusion, the one with smaller VF MD will be selected for randomization with minimization.

### Concealment mechanism {16b}

Patients and investigators are unaware of treatment allocations and have no access to the randomization sequence and codes, which are stored in a password-protected file in a computer. The NR and placebo tablets are in identical appearance and uniformly packaged.

### Implementation {16c}

The principal investigator will enroll participants. Two masked research technicians will generate the allocation sequence with randomization by minimization and assign participants to interventions.

## Assignment of interventions: blinding

### Who will be blinded {17a}

The attending ophthalmologists, the participants, the outcome assessors, and data analysts will be blinded after assignment to intervention.

### Procedure for unblinding if needed {17b}

The blinding will be maintained until a serious adverse event occurs. Unblinded participants will exit the trial and the ocular and/or medical conditions will be managed accordingly. The management results will be recorded on the clinical report form and reported to the Hong Kong Hospital Authority Cluster Research Ethics Committee.

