### Methods in analysis to handle protocol non-adherence and any statistical methods to handle missing data {20c}

Data will be analyzed on an intention-to-treat basis to include all patients who receive the randomized treatment and have at least two follow-up visits. Multiple imputation by chained equations (MICE) algorithm will be applied for estimation of missing data [28].

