## Oversight and monitoring

### Composition of the coordinating center and trial steering committee {5d}

The coordinating center is located at the University of Hong Kong Glaucoma and Optic Nerve Diagnostic Center. The trial steering committee is directed by the principal investigator and includes two independent researchers and one statistician, who are not part of the same institution as any of the members of the study team. The trial steering committee is responsible to ensure the protocol is implemented as planned, review study progress on a regular basis, and uphold good clinical practice at all times. The coinvestigators, research assistants, and technicians of the trial will be responsible for all aspects of the logistics and organization of the trial.

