### Adverse event reporting and harms {22}

Adverse events will be checked by the investigators at every follow-up visit (i.e., every 2 months). Any adverse event, whether they are related to the study or not, will be recorded in the adverse effect report form provided by the Hong Kong Hospital Authority using standard adverse event language. A serious adverse event will be reported to the Hong Kong Hospital Authority Research Ethics Committee within 24 h of the event. The principal investigator will be responsible to follow the management of the serious adverse event until resolution or conclusion. The investigators and the trial steering committee will determine whether an adverse event or serious adverse event is related to the study drug.

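### As worded, any serious adverse event ends blinding and participation, which stops OCT and visual field follow-up even after unrelated events and may put the code break before the relatedness judgement

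*Protocol article*

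**What the plan says.** All references are to the protocol article.

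- **Trigger.** Section {17b} says "The blinding will be maintained until a serious adverse event occurs. Unblinded participants will exit the trial". It does not ask whether the event is related to treatment or whether its management needs the code.
- **Consequence.** Exit follows directly from unblinding. The only later information that the section names is in "The management results will be recorded on the clinical report form".
- **Listed exits.** Section {11b} gives three safety endpoints that lead to leaving the study: VF progression, loss of visual acuity, and raised IOP on two visits. It also allows withdrawal at will. An SAE is not listed.
- **Relatedness.** Section {22} records every adverse event whatever its cause and then says "The investigators and the trial steering committee will determine whether an adverse event or serious adverse event is related to the study drug". Section {5d} adds that "The trial steering committee is directed by the principal investigator and includes two independent researchers and one statistician".
- **Masking in general.** Section {17a}: "The attending ophthalmologists, the participants, the outcome assessors, and data analysts will be blinded after assignment to intervention". Section {16b} says that investigators cannot reach the codes.
- **Analysis.** Section {20c}: "Data will be analyzed on an intention-to-treat basis to include all patients who receive the randomized treatment", provided that they have at least two follow-up visits. Missing data are to be imputed by chained equations.
- **Sample size.** Section {14} plans 56 patients per arm and 125 in total, allowing for a 10% default rate.

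**The concern.** The rule runs three things together: the event, the code break, and the end of participation. They need not coincide. An event such as an injury or an elective admission can be serious without raising any question about the capsules, and a patient who stops capsules or is unblinded can often still attend for imaging.

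Two consequences follow.

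1. **Primary outcome data.** OCT and VF readings after the event are not collected, so they become missing and go to imputation. Follow-up visits fall at 1 month, 4 months and every 2 months after that. A patient who exits before the 4-month visit therefore has at most one follow-up visit and leaves the analysis set altogether. If SAE rates differed by arm, this loss would too; nothing in the article shows that they will.
2. **Relatedness.** If blinding ends when the event occurs, attribution can come after the code break. A judgement made with the arm known is open to bias.

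**Working it through.** **The sections side by side**

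| Question | {11b} | {17b} | {20c} | {22} |
|---|---|---|---|---|
| Does an SAE end participation? | Not listed | Yes, through unblinding | – | Not stated |
| Is relatedness a condition? | – | No | – | Judged, order not stated |
| Do OCT/VF visits continue? | – | Not stated; participant exits | Imputation for missing data | – |

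Sections {11b} and {17b} give different lists of exit routes. Section {17b} makes data missing that {20c} then has to impute.

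**The plan's own sample size first**

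Inputs from {14}: slope variance 1.39 (μm/year)², residual variance 3.83 μm², difference 0.7 μm/year, power 80%, alpha 5% (two-sided reproduces the figure). The schedule has 19 scans: three each at 0, 1 and 24 months, and one at each of months 4, 6, …, 22.

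- Sxx = Σ(t − t̄)² = 10.69 year².
- Per-patient slope variance = 1.39 + 3.83/10.69 = 1.748.
- n per arm = 2 × 1.748 × (1.960 + 0.842)² / 0.7² ≈ 56.01, matching the stated 56.
- 112 / 0.90 = 124.4, rounded up to 125, which also matches.
- Margin: 125 × 0.90 = 112.5 against 112 needed, so there is almost none.

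**What an exiting patient still contributes**

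Slope information relative to a completer = 1.748 / (1.39 + 3.83/Sxx up to exit).

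- Exit at 12 months: the variance is 4.22, so the patient keeps 1.748/4.22 = 41%.
- Averaged over exit months 2 to 23, weighted equally: 42%.

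**Power under assumed SAE exit rates**

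The article gives no SAE rate. Assume that a fraction f exits, spread evenly over follow-up and in addition to the 10% default. The number per arm after default is 62.5 × 0.9 = 56.25. The effective number is 56.25 × (1 − f × 0.58) with earlier scans kept, and 56.25 × (1 − f) if exited patients contribute nothing. Power = Φ(0.7/√(2 × 1.748/n) − 1.960).

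| f | Patients of 125 | Effective n per arm, scans kept | Power, scans kept | Power, nothing contributed |
|---|---|---|---|---|
| 0% | 0 | 56.25 | 80.2% | 80.2% |
| 4% | 5 | 54.9 | 79.2% | 78.5% |
| 10% | 12.5 | 53.0 | 77.8% | 75.9% |
| 16% | 20 | 51.0 | 76.2% | 73.0% |

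The last column is a bound and not the planned analysis, because {20c} keeps anyone with two follow-up visits.

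**The case against.** The strongest reply has five parts.

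- **The bias in relatedness is inferred.** Section {17b} does not say who receives the code or when, {16b} denies investigators access to it, and the steering committee includes independent members. This stands. A reader might infer that attribution will be made unblinded and is therefore biased; the article supports only a risk of that. Nor does it give relatedness any special rank among the safety results. All events are recorded whatever their cause, and a comparison of all SAEs by arm does not depend on attribution.
- **{17b} is an exception to {17a}, not a contradiction of it.** This also stands. The general masking statement and a stated exception can coexist.
- **The data are not all lost.** Correct. Scans before the event stay in for anyone with two follow-up visits, and imputation covers the rest. Imputation, however, replaces readings that could have been taken.
- **The power loss is small and rests on an assumed rate.** Correct. The 10% default may already cover these exits, in which case planned power does not change. A reader might infer that 125 is too few; the documents do not show that.
- **A condensed article leaves procedure to the full protocol.** This has force for the order of attribution and code break, and for who holds the code. It does not answer the main point, because {17b} is not silent: it states a trigger and a consequence. A milder reading, that unblinding is only permitted after an SAE, is possible, but the text does not say so.

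**Conclusion.** The point holds as a defect in the wording of {17b}. An unconditional chain from SAE to unblinding to exit stops outcome collection where that may be unnecessary, adds an exit route missing from {11b}, and works against the intention-to-treat aim in {20c}. The unmasked relatedness judgement is a possibility that the rule leaves open and not an established fault.

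The statistical cost is modest: about 1 to 4 percentage points of power, under an assumed 4% to 16% exit rate that is additional to the 10% default, with exits spread evenly and earlier scans kept. It is not an error in the sample size. The case for change rests on the procedure and on how cheaply it can be improved.

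**What to change.** Reconcile {11b}, {17b}, {20c} and {22} so that they agree on whether an SAE in itself ends participation. In particular:

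- In {17b}, state that unblinding or stopping study capsules does not by itself end the scheduled OCT and VF visits for patients who agree to continue.
- In {17b} and {20c}, state that data from those visits stay in the intention-to-treat analysis.
- In {22}, state that relatedness is recorded before any code break, by assessors who do not know the arm.

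Whether a given event calls for a code break or for stopping capsules remains a clinical decision, and nothing here prescribes it.

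The cost is protocol wording plus visits that are already on the schedule. There are two small downsides: some patients will decline further visits, and some later readings will be taken with the arm known.

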## Data collection and management

### Plans for assessment and collection of outcomes {18a}

Patients will receive a clinical examination, OCT imaging of the RNFL, and VF testing at baseline, 1 month, 4 months, and then every 2 months for 24 months. Three repeated OCT and VF measurements will be collected at the baseline, 1-month, and 24-month visits.

#### Clinical examination

Clinical examination includes slit-lamp biomicroscopy of the anterior and posterior segments and Goldmann applanation tonometry. Two IOP readings will be obtained to calculate the mean. A third reading will be obtained if the difference between the first two is > 2 mmHg and the median is recorded. Axial length will be measured with partial coherence laser interferometry (IOLMaster, Carl Zeiss Meditec). Subjective and objective refraction will be performed at the screening and the last follow-up visits. Central corneal thickness will be measured with anterior segment optical coherence tomography (CASIA2, Tomey, Japan). Dilated fundus examination for color optic disc stereophotography will be performed at the screening visit and then yearly.

#### Optical coherence tomography imaging

The RNFL will be imaged with the Cirrus HD-OCT (Carl Zeiss Meditec, Dublin, USA) for comparison of the rates of RNFL thinning (primary outcome measure) between treatment groups. The RNFL-GCIPL will be imaged by the Triton OCT (Topcon, Tokyo, Japan) to determine the time to progressive RNFL-GCIPL thinning detected by TPA for an individual eye (secondary outcome measure). Low test-retest variability of Cirrus HD-OCT and Triton OCT measurements has been shown [26, 27]. RNFL-GCIPL thickness data of individual pixels in serial RNFL-GCIPL thickness maps collected over 24 months will be exported for TPA [17, 18, 20]. Trend-based Progression Analysis performs pixel-by-pixel linear regression analysis between RNFL-GCIPL thickness and time and determines progressive RNFL-GCIPL thinning after registering and aligning serial OCT scans in corresponding retinal locations of an eye. To minimize type I errors consequential to multiple testing in an eye, the RNFL-GCIPL thickness maps will be condensed from 512 × 256 pixels to 128 × 64 superpixels with a false discovery rate (FDR) controlled at 5%. Images with a poor signal-to-noise ratio, motion artifact, poor centration, segmentation error, or missing data (e.g., blinking) will be discarded; re-scanning will be performed in the same visit. Peripapillary and macular inner retinal vessel density will be measured with OCT angiography.

